### Qualitative sub-study data collection

The nested qualitative sub-study investigates mental health staff experiences of implementing recovery-oriented practices following the PULSAR intervention and the challenges involved within Australian mental health settings; it also seeks to explore consumer views of how their recovery has been supported in services where this staff training intervention has taken place. Two semi-structured interview guides for use in staff interviews and consumer interviews were developed, informed by literature on recovery-oriented practice, consumer and service provider expertise within the PULSAR Qualitative Research Steering Group and consultations with PULSAR’s LEAP. These interview guides are used to conduct face-to-face or telephone interviews with mental health staff three to 4 months following the PULSAR training, and with consumers five to 6 months following the PULSAR training. Staff interviews occur prior to consumer interviews on the basis that staff are likely to be aware of their own efforts to implement changes to practice before these become as evident to consumers. Interviews with staff initially explore their understanding of recovery-oriented practice and experiences and challenges encountered in implementing a recovery-oriented framework at a service level. Subsequent interviews will invite participating staff to reflect on the de-identified interview themes, and on facilitators and barriers to implementing recovery-oriented practice in their service settings in an interview or focus group discussion. Similarly, initial face-to-face or telephone consumer interviews focus on their views and experiences of recovery-oriented practice in services where mental health staff have received training, with subsequent interviews inviting consumers to reflect on the de-identified interview themes and on supports for their recovery within and beyond services.

Sample size for the qualitative sub-study is determined sequentially by qualitative sampling processes to ensure diverse perspectives are sought, and to maximize the richness of data obtained, for which we anticipate at least 20–24 staff participants and 20–24 consumer participants will be recruited and interviewed from across the specialist mental health care sites. Recruitment strategies rely on staff and consumers opting into the study based on a convenience sampling approach, informed by the current profile of consumers and staff at participating sites. Efforts are made through the use of varied recruitment strategies including flyers and onsite visits by the researchers to ensure that a diverse range of participants are represented in the evaluation. Following the PULSAR intervention in year 2, the selection of sites, specialist mental health staff and consumers to participate in the qualitative sub-study will be guided by the extent and depth of data gathered in the first year (e.g., whether some service types are under-represented; whether consumers on Community Treatment Orders or staff working with these service users have been recruited).

All qualitative data are audio-recorded (subject to participant consent) or documented in handwritten notes, then transcribed for coding and analysis. Coding will employ both inductive reasoning and an explicit theoretical lens [48]. Thus, qualitative data will be coded and analysed, using a constant comparative method, to identify thematic similarities and differences in participants’ views within and across participant groups. Further, given the PULSAR intervention is informed by CHIME and the REFOCUS recovery-promoting practices (14,29), this theoretical framework will also be used for coding so as to identify how these concepts and practices are spoken about and understood by participants. All transcribed data are de-identified and along with all other PULSAR data are stored in password-protected files within the restricted access electronic files of the PULSAR site.

#### Process evaluation data collection

Given that the recovery-oriented practice involves facilitating a process of change, a process evaluation is crucial to offer explanatory variables that may influence the outcome measures [49]. The nested process evaluation will use quantitative and qualitative data to identify contextual and organisational factors that influence the effectiveness of the intervention.

The process evaluation will provide additional data relating to clusters, drawing on the PARIHS framework dimensions of evidence, context and facilitation [32]. These data can be examined further in regression and other analyses to estimate the extent to which dimensions of readiness for, exposure to, and engagement in the PULSAR program are associated with differentials in outcome measures. The process evaluation study design adopts the recommendations of Moore et al. [50] and acts on the advice of Bhanbhro and colleagues [51] in ensuring our approach is informed by theory and evidence. The interventions in PULSAR seek to change services’ orientation to recovery-oriented practice through influencing the behaviour of clinical staff and adapting the systems in which they work. As Chen and Rossi [52] suggest, we use a theory-driven evaluation approach which is not dependent on a single outcome measure to confirm or refute the effectiveness of the intervention.

Following the guidelines provided by Moore et al. [50], the process evaluation will focus on collecting data that has the potential to surface explanatory variables in the complex path between intervention and outcomes. The theoretically grounded research questions include:What is the role of contextual factors (leadership/support for innovation/readiness for change/organisational support for change/commitment to change and perceived supervisor support for recovery orientation practice) on the adoption of the training and patient outcomes?How does dosage (number of people trained and still working at the facility/number of people attending PALS and still practicing) affect attitude to and uptake of recovery-oriented practice?What is the role of clinical context (Primary or Secondary Care/Community or Acute) on attitudes to and adoption of the intervention and client outcomes?What is the relationship between pre-existing engagement in recovery-oriented practice, on attitudes to training, evaluation of training and transfer of training?

### Statistical analysis

#### Main analysis plan for cRCT

The primary analysis involves evaluating the PULSAR training intervention at the consumer level by examining the QPR data from consumers, see Table 1. The planned data collection schedule has three main periods called T0, T1 and T2, see Fig. 1. Baseline (T0) data collection occurs in the year prior to and 3 months after the step 1 intervention is delivered. The first 3 months after intervention delivery is a period still considered relevant for baseline data collection based on the Kirkpatrick training evaluation model [53] which considers that the embedding of practice change requires a minimum of 9 months after intervention is delivered, including 3 months for consolidation and 6 months for implementation. In the next period called step 1, (T1), data collection occurs during the following 12 months. Then in the next period called step 2, (T2), data collection occurs during the following 12 months. During both T1 and T2 periods, data collection at individual clusters occurs at a minimum of 9 months after the intervention was delivered to ensure embedding of intervention practices and principles, see Fig. 1.

Descriptive statistics will be used to summarize the characteristics of the clusters at baseline and consumer-level variables at time of data collection (see Table 5). Cluster-level variables are those used in the stratified randomization, which are seven types of organizational variations (see Table 2), plus the intervention status of the cluster and the time since (or before) the start of the intervention. The ICC will be calculated and reported.

The analysis of data in a stepped-wedge cRCT is most suitably analysed in mixed-effects models [54]. The primary analysis examines the effect of PULSAR on the primary outcome (consumer-level QPR scores) using a linear mixed-effects model state ‘on an intention-to-treat basis’. The model will include intervention status and time as fixed effects and clusters and consumers as random effects. Normally step one is just to examine intervention – control group differences controlling for cluster, before including covariates. An a priori model-fitting analysis strategy will involve both univariate and multivariable models to be developed based on baseline consumer and cluster-level variables considered statistically significant (*p* < 0.10) or clinically important (e.g., age, sex), see Table 5, and included in the model as fixed. Model fit will be examined by comparing AIC values.

Secondary analyses will examine the effect of PULSAR on secondary outcomes (WEMWBS and INSPIRE) using a linear mixed-effects models to compare the intervention and control periods (pre-intervention).

Estimated intervention effects will be reported as the mean outcome difference for continuous outcomes and Odds Ratio for binary outcomes between intervention and control periods. This can be described as a meta-analysis approach as (in the case of continuous data) the mean change in each cluster will be standardized by using the variance of the outcome measure within that cluster. The estimated intervention effects will be reported with 95% Confidence Intervals and *p* values. Analysis will be conducted using Stata V.14, StataCorp. Stata Statistical Software: Release 14. College Station, TX: StataCorp LP, 2015.

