**Methods:**

The mixed methods design incorporates a two-step stepped-wedge cluster randomized controlled trial (cRCT) examining cross-sectional data from three phases, and nested qualitative and process evaluation sub-studies. Participating specialist mental health care services in Melbourne, Victoria are divided into 14 clusters with half randomly allocated to receive the staff training in year one and half in year two. Research participants are consumers aged 18–75 years who attended the cluster within a previous three-month period either at baseline, 12 (step 1) or 24 months (step 2). In the two nested sub-studies, participation extends to cluster staff. The primary outcome is the Questionnaire about the Process of Recovery collected from 756 consumers (252 each at baseline, step 1, step 2). Secondary and other outcomes measuring well-being, service satisfaction and health economic impact are collected from a subset of 252 consumers (63 at baseline; 126 at step 1; 63 at step 2) via interviews. Interview-based longitudinal data are also collected 12 months apart from 88 consumers with a psychotic disorder diagnosis (44 at baseline, step 1; 44 at step 1, step 2). cRCT data will be analyzed using multilevel mixed-effects modelling to account for clustering and some repeated measures, supplemented by thematic analysis of qualitative interview data. The process evaluation will draw on qualitative, quantitative and documentary data.

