**Fig. 1 Fig1:**
[figure not shown]
PULSAR Specialist Care study design and planned timeline Notes. Indicated at the *bottom* is the study year. The two-step cluster randomise control trial is shown: half the clusters receive the intervention in step 1 and the remaining clusters receive the intervention in step 2. For a summary of the study evaluations see Table 1

**Table 1 Tab1:** Evaluation plan for the PULSAR Specialist Care study

	Sub-study name	Evaluation design	Unit of analysis	Number	Number at each time point	Number in each cluster at each time point	Detectable differences		
							Primary outcome, QPR	Secondary outcome, WEMWBS	Secondary outcome, INSPIRE
cRCT (quantitative data)	Stream 1 (primary analysis)	cross-sectional cRCT (complete step-wedge)	Consumers (mail-out)	756	252 at baseline 252 at step 1 252 at step 2	18	6.34 (medium effect)	NA	NA
	Stream 2	pre- and post-intervention (incomplete step-wedge)	Consumers (interviews)	252 (stream 1 subset)	63 at baseline 126 at step 1 63 at step 2	9	7.68 (medium effect)	4.80 (medium effect)	7.72 (medium effect)
	Stream 3	longitudinal, (same participant, 12-mths apart pre- and post-intervention)	Consumers with diagnosis of psychosis (interviews)	88 (stream 2 subset)	44 at baseline & step 1 44 at step 1 & step 2	6–7	10.94 (medium-large effect)	6.84 (medium-large effect)	11.28 (medium-large effect)
Nested Qualitative study (qualitative data)			Consumers Staff	20–24 20–24	10–12 at step 1 10–12 at step 2	Nested sub-study examining qualitative data collected in study interviews and focus groups			
Nested Process evaluation (both quantitative & qualitative data)			Consumers & staff	The process evaluation assesses a specific set of qualitative, quantitative and documentary data relating to each cluster.					

Notes. The primary analysis examines the primary outcome– the Questionnaire about the Process of Recovery (QPR) - collected in the two-step stepped-wedge cluster randomized controlled trial (cRCT). A subset of consumers in the cRCT participate in study interviews where secondary outcomes measuring well-being, service satisfaction and health economic impact are collected In a yet another subset in the cRCT, longitudinal data are collected via interviews that are 12 months apart from consumers with a diagnosis of a psychotic disorder. Qualitative and process evaluation sub-studies are nested within the overarching cRCT and include information from consumers and staff.

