### Sample size

The primary analysis examines QPR data from consumers in the cRCT (stream 1) and requires a total sample size of 756 consumers from 14 clusters over 3 years (see Table 1). This will be sufficient to detect a medium effect size representing a change in QPR score by 6.34, see Table 1. Secondary analyses that examine data from a subset of stream 1 consumers who participate in stream 2 of the cRCT, requires a total sample size of 252 consumers over the study period. This will be sufficient to detect medium effect sizes in the QPR and two secondary outcome measures (WEMWBS and INSPIRE), see Table 1. Additional secondary analyses to examine longitudinal data from a subset of stream 2 consumers who participate in stream 3 of the cRCT, requires a total sample size of 88 consumers over the study period. This will be sufficient to detect medium-large effect sizes in the QPR and WEMWBS and INSPIRE, see Table 1.

Sample size calculations were based on 14 clusters; intracluster correlation coefficient (ICC) of 0.05; significance level set at 0.05; power of 0.80; and available published [34, 36, 45] and unpublished (INSPIRE) data about distribution properties. All sample size calculations indicate the minimum number of participants we aim to recruit and were done using Stata statistical software *stepped-wedge* [46] Version 11, StataCorp. 2009.

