##### Modified recruitment protocol

Due to this low response rate, the consumer recruitment protocol went through a series of adaptations to facilitate greater engagement and flexibility of recruitment strategies. The primary mode of recruitment through mail out was modified to a) allow mail outs of letters of invitation to complete and return the Stream 1 survey form to all eligible consumers of the participating services from each cluster site; b) replace the 10-page PICF in the survey pack with a simple one-page consent to be contacted for a face-to-face interview form, thus requiring implied consent only for return of the mailed questionnaire and demographic form; and c) provide a $10 shopping voucher for all returned questionnaires where contact details are provided.

A range of secondary recruitment strategies to promote consumer response to the mail outs were added and flexibly employed according to the needs of sites. Strategies include, for example, having researchers, including consumer researchers, present at sites to speak about PULSAR; the use of publicity materials such as advertisements, posters or PULSAR-branded materials; and direct contact with clinicians and consumers at participating sites. Considerable care was taken to ensure, as far as reasonably possible, that recruitment strategies were consistent across time points at participating clusters.

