### cRCT data collection

In stream 1 of the cRCT, cross-sectional data are collected from mail-outs to consumers at three time points, see Table 1. Stream 1 participants can return a completed QPR/demographic survey anonymously in a provided reply-paid envelope addressed to the researchers if they wish. However, they are invited to provide their contact details on a separate one-page “Participant Contact and Consent Form” if they would like to be mailed a $10 shopping voucher. Participants can additionally indicate on the Participant Contact and Consent Form if they are willing to volunteer for other parts of the PULSAR project, such as a face-to-face interview, by signing a “Consent to Future Contact” section.

In streams 2 and 3 of the cRCT, data are collected in structured face-to-face interviews from a subset of stream 1 consumers who consent to future contact, see Table 1 and earlier section *Levels of consumer participation*. A pool of around 12–14 casual research assistants conduct the face-to-face interviews. Prior to conducting interviews, all research assistants attend a compulsory 2 day training workshop facilitated by senior PULSAR researchers. This training is conducted annually prior to commencement of fieldwork each year to train new staff and maintain the skills of continuing research assistants. Training modules include: research interviewing skills; research interviewing from the consumer perspective; risk assessment, including consumer safety, risk management, and distress management; staff safety, including aggression and risk management; communication skills; research ethics; home visit protocols; and blindness. The first two interviews with consumer participants are supervised by a senior PULSAR researcher, and research assistants are provided with verbal and written feedback at the end of each interview.

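### The primary model leaves no room for cluster-by-period variation, so if cluster deviations drift between waves its standard error is too small; the consumer random effect needs linked repeat surveys

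*Protocol article*

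**What the plan says.** The protocol article fixes the primary model under Main analysis plan for cRCT: intervention status and time are fixed effects, with "clusters and consumers as random effects". It names no cluster-by-period term, correlation decay or robust variance.

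The primary data are stream 1. Table 1 describes them as cross-sectional and complete, with "252 at baseline 252 at step 1 252 at step 2", or 18 per cluster at each time point. On planning, the Sample size section says: "Sample size calculations were based on 14 clusters; intracluster correlation coefficient (ICC) of 0.05; significance level set at 0.05; power of 0.80". It gives one ICC, no correlation between periods and no QPR standard deviation, and arrives at a detectable difference of 6.34.

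Two further statements bear on the consumer effect. Under cRCT data collection: "Stream 1 participants can return a completed QPR/demographic survey anonymously in a provided reply-paid envelope addressed to the researchers if they wish". The abstract, however, describes "multilevel mixed-effects modelling to account for clustering and some repeated measures". Under Modified recruitment protocol, invitations go "to all eligible consumers of the participating services from each cluster site", so the same person can be invited in more than one wave.

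**The concern.** In a cross-sectional stepped wedge, the treatment contrast rests partly on comparing a cluster with itself in another period. A cluster-only random intercept says that two respondents from the same cluster are equally correlated whether surveyed in the same wave or two years apart. In other words, the cluster autocorrelation (CAC) is exactly 1.

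The article gives reasons to doubt this:

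- Staff movements are expected and are tracked every three months (Intervention dosage), and turnover is reported as a problem in the predecessor trial (REFOCUS).
- Crisis teams and PARC services are short-term (Table 2) and eligibility requires contact within three months, so their respondents will largely change between waves.
- Secondary recruitment strategies were adapted to each site's needs.

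If clusters do drift in their own ways, the model treats part of that drift as independent individual error. The primary standard error is then too small and 6.34 is optimistic.

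The consumer effect is a separate matter. With one survey per person it cannot be told apart from residual error, and anonymous returns cannot be linked across waves.

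**Working it through.** **Inputs.** From the article: 14 clusters (7 per sequence), 3 periods, m = 18 per cell, ICC 0.05, alpha 0.05, power 0.80. Check: 14 × 18 = 252, and 252 × 3 = 756. Assumed: a two-sided test, time fitted as three period effects, and CAC (range 0.5 to 1). The total variance is scaled to 1.

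**Formula.** Let τ² = ICC × CAC, and let s² = (1 − ICC)/m + ICC × (1 − CAC) be the variance of a cell mean given its cluster. With treatment indicators (0,1,1) and (0,0,1):

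- U = 7×2 + 7×1 = 21
- W = 0² + 7² + 14² = 245
- V = 7×4 + 7×1 = 35

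Var = 14 s²(s² + 3τ²) / [(14U − W)s² + (U² + 42U − 3W − 14V)τ²] = 14 s²(s² + 3τ²) / [49 s² + 98 τ²]

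**Reproducing 6.34 (CAC = 1).** s² = 0.95/18 = 0.05278 and τ² = 0.05. Var = 14 × 0.05278 × 0.20278 / (2.5861 + 4.9) = 0.02001, so SE = 0.1415 SD. The detectable difference is (1.960 + 0.842) × 0.1415 = 0.3963 SD, and 6.34/0.3963 gives SD = 16.0. As a cross-check, the stream 2 figure of 7.68 also gives 16.0 under a simple design effect with N = 252 and 18 per cluster: 2.802 × √(4 × 1.85/252) = 0.480, and 7.68/0.480 = 16.0. The 6.34 thus fits a cluster-only calculation, but this is a consistency check because the SD is back-solved.

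**Adding cluster-by-period variance (ICC 0.05).** For CAC 0.8, s² = 0.06278 and τ² = 0.04. Var = 14 × 0.06278 × 0.18278 / (3.0761 + 3.92) = 0.02296, so SE = 0.1515 and the detectable difference is 0.4245 × 16.0 = 6.79. The other rows follow in the same way.

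| CAC | Correct-model SE (SD units) | Detectable difference | Power at 6.34 |
|---|---|---|---|
| 1.0 | 0.1415 | 6.34 | 80% |
| 0.9 | 0.1467 | 6.58 | 77% |
| 0.8 | 0.1515 | 6.79 | 74% |
| 0.5 | 0.1630 | 7.30 | 68% |

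**What the stated model would report.** The table compares the SE claimed by a cluster-only fit with the true SE of its estimate. Approximate type I error is 2[1 − Φ(1.96 × ratio)].

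| CAC | Claimed SE | True SE | Ratio | Type I, formula | Type I, simulated REML with z | Type I, simulated REML with t (24 df) |
|---|---|---|---|---|---|---|
| 1.0 | 0.1415 | 0.1415 | 1.00 | 5.0% | 5.3% | 4.4% |
| 0.9 | 0.1413 | 0.1468 | 0.96 | 5.9% | 6.1% | 5.2% |
| 0.8 | 0.1410 | 0.1518 | 0.93 | 6.9% | 7.2% | 6.2% |
| 0.5 | 0.1400 | 0.1645 | 0.85 | 9.5% | 9.5% | 8.3% |

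The simulations had no treatment effect, with 1,500 trials per setting for z and 20,000 for t. With a cluster-by-period intercept, REML and t on 24 df, rejection is 3.7%, 4.6% and 4.8% at CAC 1.0, 0.8 and 0.5. At ICC 0.10, the cluster-only z test rejects 7.5%, 8.8% and 14.8% at CAC 0.9, 0.8 and 0.5.

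**Consumer effect.** With one record per person, only the sum of consumer and residual variance enters the covariance matrix. Splits of 0.60/0.35, 0.20/0.75 and 0/0.95 all sum to 0.95 and give the same matrix (log-determinant −1.4238 for 54 records in one cluster). If the 88 stream 3 pairs (up to 176 records) were in the primary dataset, the within-person correlation r could be estimated, with SE about (1 − r²)/√88. For r = 0.5 that is 0.75/9.38 = 0.08.

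**The case against.** A reader might infer that the consumer effect cannot be estimated at all. The article does not support that. The abstract anticipates some repeated measures, anonymity is optional, respondents who want the voucher give contact details, and Table 1 nests stream 3 (88 people interviewed twice) within stream 2 and stream 2 within stream 1. Linked repeats would identify the consumer variance. What stands is that the article does not say whether those repeats are in the primary dataset, and that single or unlinked surveys carry no information on it.

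A reader might also infer that the consumer term is what makes the intervals too narrow. It is not: when unidentified, it is absorbed into the residual.

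Nor does the model hold each cluster's mean fixed. Time is a fixed effect, so means follow the common trend; only the cluster's deviation from it is constant. Some sources of drift are partly addressed: covariates such as age and sex may enter the multivariable models, dosage enters a sensitivity analysis, and care was taken to keep recruitment consistent across time points. These measures reduce the likely drift but do not make CAC equal to 1. A consumer effect does not replace the missing term either, because it captures correlation within a person rather than a shift shared by everyone in a cluster in one wave.

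Finally, the article specifies neither the estimation method nor the reference distribution, and an analysis plan may do so. Part of the inflation under z tests comes from that choice, which is why the t-test column is shown: at CAC 0.9 the problem then almost disappears.

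**Conclusion.** The concern holds in conditional form. The article states a primary model with no cluster-by-period variation, and its 6.34 matches a calculation that assumes none. If CAC is below 1, the standard error is too small: by about 4%, 7% and 15% at 0.9, 0.8 and 0.5, with type I error of about 6%, 7% and 10% under z tests or 5%, 6% and 8% under REML with t tests. The detectable difference rises to about 6.6, 6.8 and 7.3.

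It would go too far to say that the type I error of this trial exceeds 5%. The article gives no CAC, and at 1 the stated model is adequate. The figures also rest on the planned ICC of 0.05, a back-solved SD of about 16 and equal cells of 18. The effect is modest at that ICC and larger if the ICC is higher.

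The consumer effect is a secondary point of clarity: it is estimable only from linked repeats, and the article leaves open whether the primary dataset contains any.

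**What to change.** 1. Add a random intercept for cluster-by-period to the primary model, beside the cluster intercept. Fit by REML with a small-sample degrees-of-freedom correction such as Kenward-Roger, given 14 clusters.
2. State which QPR records enter the primary dataset, in particular whether stream 3 second interviews and repeat mail respondents count. Keep a consumer random effect only where repeats are linked. Dropping it outright would ignore the repeats that the abstract expects.
3. State that 6.34 assumes no cluster-by-period variation, and give about 6.6 to 7.3 as an illustrative range for an autocorrelation of 0.9 to 0.5, with the SD used.

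The cost is a change of wording, somewhat wider intervals and a less favourable detectable difference. No extra data collection is needed.

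### Adjusted models are chosen by AIC with only 14 clusters: if the maximum-likelihood fit containing cluster type is the one reported, the 5% test rejects about 7–9% of the time in stream 1

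*Protocol article*

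**What the plan says.** In the protocol article, the section Main analysis plan for cRCT sets a linear mixed model with intervention status and time as fixed effects and clusters and consumers as random effects. Multivariable models follow. Covariates that reach p < 0.10 or are judged clinically important are taken from Table 5 and entered as fixed effects. Then: "Model fit will be examined by comparing AIC values". On reporting: "The estimated intervention effects will be reported with 95% Confidence Intervals", together with p values.

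Table 5 lists the cluster types among the variables available for these models. The same section says: "Cluster-level variables are those used in the stratified randomization, which are seven types of organizational variations". Table 2 shows the seven strata, each holding two clusters. The Sample size section states "Sample size calculations were based on 14 clusters", with "intracluster correlation coefficient (ICC) of 0.05" and "significance level set at 0.05; power of 0.80".

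Neither the estimator (maximum likelihood or REML) nor a reference distribution is named for the reported effects.

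**The concern.** AIC values from models with different fixed effects are comparable only under maximum likelihood (ML). ML estimates the cluster variance as if the fixed effects were known. That matters little for two or three period terms. It matters when six cluster-type terms are fitted to 14 clusters, because about half the between-cluster information has then been used up. The cluster variance comes out too small, often zero, and the standard error of the intervention effect shrinks with it. A normal quantile also ignores that the variance was estimated.

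At stake are the width of the confidence intervals and the false-positive rate in the adjusted models, in particular those that respect the stratified randomization.

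**Working it through.** **Inputs.**
- 14 clusters in 7 pairs (Sample size; Table 2).
- Two steps, "half randomly allocated to receive the staff training in year one and half in year two" (abstract, Methods).
- Stream 1 QPR data "collected from 756 consumers (252 each at baseline, step 1, step 2"), so 252/14 = 18 per cluster and period.
- ICC 0.05, alpha 0.05 (taken as two-sided), power 0.80 (Sample size).
- The SD of the QPR is not given. It does not affect the error rates.

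**Step 1: the plan's own figure.** Use the stepped-wedge variance for a random cluster intercept with fixed periods, on the SD scale. Here τ² = 0.05, s² = 0.95/18 = 0.05278, I = 14, T = 3, U = 21, W = 7² + 14² = 245, V = 7·4 + 7·1 = 35:

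Var = I s²(s² + Tτ²) / [(IU − W)s² + (U² + ITU − TW − IV)τ²]
= 14 × 0.05278 × 0.20278 / (49 × 0.05278 + 98 × 0.05) = 0.1498/7.486 = 0.02001, so SE = 0.1415.

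Detectable difference = (1.960 + 0.842) × 0.1415 = 0.396 SD. This equals the stated 6.34 if the SD is 16.0 (an implied value). The planning figure is therefore reproduced, with normal quantiles and no cluster-type terms.

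**Step 2: size of the variance bias.** A cluster mean over three periods has variance 0.05 + 0.95/54 = 0.05 + 0.0176 = 0.0676. Seven type means leave 7 of 14 degrees of freedom (about six once the intervention contrast is counted), but ML still divides by 14. Roughly, 0.0676 × 7/14 = 0.0338, and 0.0338 − 0.0176 = 0.016, about a third of the true 0.05. Simulation agrees. The true variance ratio is 0.05/0.95 = 0.0526. The mean estimate is 0.0171 under ML and 0.0533 under REML, and the estimate is zero in 22% and 3.5% of trials respectively.

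**Step 3: effect on the test.** Null trials were simulated with a random cluster intercept and with period and intervention fixed (10,000–20,000 per setting, Monte Carlo SE about 0.2–0.3 points). Stream 1, ICC 0.05, cluster type in the model:

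| Fit, ±1.96 | Mean SE | Actual SD of estimate | 1.96 × SE/SD | Implied error | Counted error |
|---|---|---|---|---|---|
| ML | 0.1310 | 0.1505 | 1.706 | 8.8% | 9.0% |
| REML | 0.1390 | 0.1441 | 1.891 | 5.9% | 5.9–6.0% |

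REML with a t reference on 26 df (illustrative) gives 5.0%.

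Other settings, ML with ±1.96:
- Stream 1 with cluster type, by ICC: 7.0% at 0.01, 8.1% at 0.02, 8.4% at 0.10, 6.7% at 0.20. Taken together, about 7–9%.
- Stream 1 without cluster type: 5.8–5.9% at ICC 0.05, and 5.3–5.9% over ICC 0.01–0.20.
- Stream 2 (9 per cell; year-1 clusters at T0 and T1, year-2 clusters at T1 and T2) with cluster type: 10.3–10.6% in two runs, with another run giving 6.5–10% for streams 2 and 3 together. REML with ±1.96 gives about 6.3–6.4%.
- Stream 3 (6 per cell) with cluster type: 8.6–8.8%. This omits the consumer effect, so it is not the plan's full model.

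**Step 4: the selection step.** In stream 1, AIC under ML picks the six type terms in 29% of trials even when types do not differ, and in 56–87% when they do, depending on how much variance lies between types. Over the whole procedure, picked or not, the error is 7.5–9.2% in these settings. Another run gave about 6–8%, with 8.9% at ICC 0.10. Taken together, about 6–9%.

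**The case against.** **The estimator is inferred.** An AIC comparison by ML followed by a REML refit is compatible with the text and gives about 6%. Nearly all the excess therefore rests on a step the article does not state. This stands, and it makes the error figures conditional. Estimator and degrees of freedom are also commonly left to the analysis plan, so their absence alone would be no finding. What the article does fix is data-driven entry of up to six cluster-level terms, judged by AIC, in a trial with 14 clusters. That choice is unsafe unless the reported inference is separated from the ML fit.

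**Cluster type is only a candidate.** This also stands. It is not in the core primary model, and the sentence naming the seven types sits in a paragraph on descriptive statistics. The primary model as first described is close to nominal.

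**Other terms matter.** If allocated step, also listed in Table 5, enters alongside cluster type, ML with ±1.96 gives 5.3% in stream 1.

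**A stronger reading is tempting:** that the plan commits to ML, so the trial's 5% test runs at 9–11%. The article does not support this. It names no estimator for the final effects and does not require cluster type. Stream 1 rates of 9–12% occur only among simulated trials in which AIC had already picked cluster type, and the unconditional rates above 10% come from stream 2.

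**Conclusion.** The point holds in conditional form. If the AIC-chosen ML fit is reported with normal quantiles, the nominal 5% test in stream 1 rejects about 7–9% of the time with cluster type in the model, and about 6–9% over the whole select-or-not procedure. Stream 2 reaches about 10%. The matching 95% intervals are too narrow. The core primary model without cluster type is at about 6% or less in stream 1, so having 14 clusters without a correction is by itself a small problem there.

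The figures assume ML with ±1.96, a random cluster intercept that is constant over periods, equal cell sizes, and an ICC near the planning value. It would be wrong to infer that the primary result as planned is invalid, or that the error is doubled in general.

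**What to change.** State three things in the analysis section:

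1. ML is used only to compare AIC values. Every intervention effect, interval and p value comes from a REML fit with Kenward-Roger or Satterthwaite degrees of freedom.
2. Cluster type, as the stratification factor, is entered by pre-specification and not by p < 0.10 or AIC.
3. Optionally, the primary result is checked with a permutation test over the 2⁷ = 128 allocations that split each stratum.

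The cost is a few sentences and modest programming. With cluster type in the model, the mean stream 1 standard error rises from 0.1310 to 0.1390 (about 6%). A t reference on 26 df (2.056 against 1.960, illustrative) widens intervals by a further 5% or so. With that reference and the planning SE, power at the stated detectable difference is Φ(2.802 − 2.056) = Φ(0.746), about 77% instead of the normal-theory 80%.
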